### Blinding

5.9

Blinding of patients and operating surgeons is not feasible due to the obvious procedural differences between FANS f‐URS and mini‐PCNL. However, radiologists who review all postoperative CT scans will be blinded to treatment allocation. Clinical follow‐up assessments will be conducted by investigators who did not participate in the surgeries. Statistical analyses will also be performed in a blinded fashion: the analyst will remain unaware of group assignments, which will only be unmasked once data interpretation is complete.

### Subject withdrawal

5.10

Participants will remain in the trial unless they choose to withdraw or are medically unable to continue. If a participant elects to withdraw, we will request permission to continue capturing relevant outcome data from their medical records. Any status changes short of complete withdrawal of consent—including loss to follow‐up—will be treated as ongoing participation, and every effort will be made to collect all scheduled outcome measures. In cases where the assigned procedure cannot be completed due to intraoperative factors (e.g., access failure in mini‐PCNL, failure of FANS placement or equipment malfunction [scope or sheath damage]), crossover to the alternative arm (FANS f‐URS ↔ mini‐PCNL) will be permitted. All crossover events will be clearly documented with reasons specified. For the primary analysis, crossover cases will be analysed according to the intention‐to‐treat (ITT) principle, while per‐protocol (PP) analyses will exclude these patients.

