### Sample size

5.11

Based on published literature, the immediate SFR for mini‐PCNL in 1–2 cm lower pole stones is approximately 85%; we therefore assume an immediate SFR of 85% for both the mini‐PCNL and FANS f‐URS arms^8^, ^17^, ^18^. A non‐inferiority margin of 8.5% has been selected, as an absolute reduction in SFR of up to 8.5% is deemed the maximum clinically acceptable loss of efficacy given the benefits of FANS f‐URS (less invasiveness, faster recovery and lower bleeding risk) and aligns with margins used in similar endourological trials.^8^ Using simulations conducted in Stata with an 80% power and an alpha level of 2.5%, the required sample size is 278 participants per group (totalling 556). To account for an anticipated 15% loss to follow‐up or withdrawal, we inflate each arm to 320 participants, yielding a final enrolment target of 640 patients.

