### Statistical analysis

5.12

Statistical analysis will be performed using SPSS software version 20.0. The primary analysis will follow the ITT principle, including all randomized participants in their assigned groups regardless of protocol adherence. A secondary PP analysis will include only those participants who complete the assigned intervention without major protocol violations, to assess the robustness of the ITT findings.

Primary and secondary outcomes will be analysed as follows: Continuous data that are normally distributed will be presented as mean ± standard deviation (x ± s), while non‐normally distributed data will be expressed as median (with interquartile ranges). For comparisons of normally distributed continuous data between groups, the independent samples t‐test will be used. The Mann–Whitney U test will be applied for comparisons of non‐normally distributed continuous data. Categorical data will be presented as frequency (rate) and analysed using the chi‐square test or Fisher's exact test. If multivariate analysis is required, multiple linear regression or logistic regression models will be employed, depending on whether the dependent variables are continuous or categorical. Statistical results will be reported as estimates with 95% confidence intervals (CIs), which will be compared to the pre‐specified non‐inferiority margin. Blinded statistical analyses will be performed, with the analyst unaware of group assignments. The group allocation code will remain concealed until the analyses and interpretation have been completed. A predefined subgroup analysis will stratify patients by IP angle (e.g. <30° vs. ≥30°) to evaluate whether anatomical variation influences comparative efficacy and safety. A mixed‐effects model or generalized estimating equations may be employed post hoc to adjust for potential clustering by study centre and assess the robustness of primary findings across sites.

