## DISCUSSION

6

This international, multicentre, randomized non‐inferiority trial is designed to address a critical gap in the management of 1–2 cm lower pole renal stones: whether FANS f‐URS can achieve SFRs comparable to mini‐PCNL, while offering the well‐documented benefits of a less invasive approach. By leveraging the combined expertise of 20 high‐volume centres, our protocol ensures both rapid patient accrual and procedural consistency, thereby enhancing the statistical power and generalizability of our findings.

The primary strength of this study lies in its rigorous non‐inferiority design with a clinically meaningful 8.5% margin, informed by expert consensus and precedent in urolithiasis research. Blinded assessment of imaging outcomes and centralized randomization further minimize bias, while a robust per‐protocol and intention‐to‐treat analysis plan will verify the stability of our conclusions. Inclusion of detailed secondary endpoints—operative time, hospital stay, pain scores, complications and quality of life—will furnish a comprehensive view of each technique's risk–benefit profile.

Nonetheless, several limitations merit consideration. First, neither patients nor surgeons can be blinded to treatment allocation, which may introduce performance or reporting bias; however, the blinding of radiologic reviewers and outcome assessors should mitigate this risk. Second, despite uniform training and monitoring, subtle differences in surgical technique or postoperative care among centres may contribute to outcome variability. Predefined subgroup analyses by IP angle and centre‐effect adjustments will help elucidate and account for these factors. Third, the non‐inferiority margin, while carefully chosen, remains an arbitrary threshold; should the observed difference approach this boundary, interpretation will require careful clinical judgement.

This trial does not incorporate a formal cost‐effectiveness or health‐economic analysis. The main reason is that reimbursement standards and device costs vary substantially across participating centres and countries, making accurate and comparable cost assessment unfeasible within the current study design. To partially address this, we will document all supplementary device use as part of the trial records, although a comprehensive economic evaluation remains outside the scope of this study and should be pursued in future research.

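### A failed procedure rescued by the other one counts as a success of the assigned arm in ITT and is dropped from per-protocol, so agreement of the two does not test technical failure

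*Protocol article*

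**What the plan says.** Section 5.10 (Subject withdrawal) permits crossover in both directions when the assigned procedure cannot be completed for intraoperative reasons. Its examples are failed percutaneous access, failed FANS placement and equipment damage. It then fixes the handling: "crossover cases will be analysed according to the intention‐to‐treat (ITT) principle, while per‐protocol (PP) analyses will exclude these patients". Every crossover and its reason is to be recorded.

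Section 5.12 makes ITT in all randomised patients primary. The per-protocol (PP) set is limited to patients who completed the assigned procedure with no major violation, and its purpose is "to assess the robustness of the ITT findings". Section 6 goes further: "a robust per‐protocol and intention‐to‐treat analysis plan will verify the stability of our conclusions".

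Section 3.1 defines the primary outcome by residual fragments on CT within 72 hours of surgery. It sets no condition on which procedure cleared the stone, and nowhere does the article count a crossover as failure of the assigned procedure.

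Section 5.7.2 bears on who crosses over. If the smallest sheath cannot be advanced, the patient is stented and has a staged f-URS two weeks later. Section 5.10 lists failed FANS placement as a ground for crossover.

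**The concern.** Section 2 asks whether FANS f-URS achieves stone-free rates (SFRs) comparable with those of mini-PCNL. A technique that sometimes cannot be completed is less effective for that reason, and here the rescue is the comparator itself.

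A patient whose FANS procedure fails, who then has mini-PCNL and is clear on the 72-hour CT, adds a success to the FANS arm in ITT. PP removes the same patient, so it conditions on the procedure having worked. Mini-PCNL failures rescued by FANS are treated in the same way.

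For this failure mode the two analyses do not check each other. One credits the rescue and the other deletes the case, and a difference between the arms in technical failure may appear in neither. At stake is a non-inferiority claim about the FANS technique that partly rests on mini-PCNL clearances, backed by a robustness statement that cannot detect this.

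**Working it through.** **Inputs from the article.** Section 5.11 gives the assumed rates ("we therefore assume an immediate SFR of 85% for both the mini‐PCNL and FANS f‐URS arms"), the margin ("margin of 8.5% has been selected"), and power and alpha ("with an 80% power and an alpha level of 2.5" per cent, read as one-sided because Section 5.12 compares a 95% CI with the margin). The evaluable number is 278 per arm.

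**Reproducing the stated sample size.** With unpooled variance, n = (1.96 + 0.8416)² × (2 × 0.85 × 0.15) / 0.085² = 7.849 × 0.255 / 0.007225 = 277.02, rounded up to 278. This matches. The chance of declaring non-inferiority at 278 per arm with equal rates is 80.1%. (After 15% loss from 320, 272 per arm remain and the figure is 79.3%, so the choice of n hardly matters here.)

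**Assumptions not in the article.** Let f be the share of FANS patients and g the share of mini-PCNL patients who cross over. Let r be the SFR after rescue, and take 85% among completers in both arms. The article gives none of f, g or r.

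**Formulas.**
- ITT arm rate: (1 − f) × 0.85 + f × r for FANS, and the same with g for mini-PCNL.
- PP arm rate: 0.85, with n reduced to 278 × (1 − f) and 278 × (1 − g).
- Crossover as failure: (1 − f) × 0.85 and (1 − g) × 0.85, all 278 kept.
- P(NI) = Φ[(0.085 + d)/SE − 1.96], where d is the FANS rate minus the mini-PCNL rate and SE is the unpooled standard error.

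**One case in full (f = 10%, g = 0, r = 85%).**
- ITT: 0.90 × 0.85 + 0.10 × 0.85 = 0.85, d = 0, SE = √(2 × 0.1275/278) = 0.0303, P(NI) = 80.1%.
- PP: FANS n = 278 × 0.90 = 250.2, d = 0, SE = 0.0311, P(NI) = 78.0%.
- Crossover as failure: 0.90 × 0.85 = 0.765, d = −0.085, so the first term is zero and P(NI) = Φ(−1.96) = 2.5%.

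With g = 0, the crossover share that uses up the whole margin is 0.085/0.85 = 10%.

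**Range of crossover rates, r = 85%.** The ITT and PP differences are 0 in every row.

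| FANS f | mini-PCNL g | P(NI) ITT | P(NI) PP | Difference, crossover as failure | P(NI), crossover as failure |
|---|---|---|---|---|---|
| 2% | 0% | 80.1% | 79.7% | −1.70 points | 59.3% |
| 5% | 0% | 80.1% | 79.1% | −4.25 points | 26.5% |
| 10% | 0% | 80.1% | 78.0% | −8.50 points | 2.5% |
| 10% | 5% | 80.1% | 77.0% | −4.25 points | 23.1% |
| 5% | 5% | 80.1% | 78.1% | 0 | 72.0% |
| 2% | 5% | 80.1% | 78.7% | +2.55 points | 92.4% |

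**Dependence on rescue success (f = 10%, g = 0).** The ITT difference is 0.10 × (r − 0.85). For r = 50%, 70%, 85% and 95% it is −3.5, −1.5, 0 and +1.0 points, with ITT P(NI) of 35%, 62%, 80% and 89%.

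The direction therefore depends on which arm fails more often, and the size in ITT depends on how well rescue works.

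**The case against.** A reader might infer that both analyses always lean towards non-inferiority. The article does not support that. Section 5.10 is symmetric and names failed mini-PCNL access among its examples. Equal failure rates cancel in the difference, and in the last row of the table the written rules hide an advantage of FANS.

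A reader might also take the 80.1% at 10% crossover as a type I error rate to set against 2.5%. It is one only if crossover is defined as failure, which the protocol does not do. For the ITT comparison as written the true difference in that case is zero, so 80.1% is ordinary power. Keeping crossovers in the assigned arm is standard ITT and answers a legitimate question, namely the result of starting with FANS.

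Making crossover-as-failure the primary endpoint would have its own weakness: the decision to cross over lies with an unblinded surgeon (Section 5.9) and would override a CT read by blinded radiologists. In addition, a rescued patient counts as a success only if clear on that CT, and under Section 5.7.2 some sheath failures go to staged f-URS and receive no comparator clearance. PP still tests other departures from protocol.

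All of this stands, and it limits the point to a conditional one. It does not remove it. Extra sensitivity analyses are often left to an SAP, but the article has itself fixed how crossovers are handled and asserts that the ITT and PP pair verifies the conclusion.

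**Conclusion.** The point holds in conditional form. If failures leading to crossover are more frequent with FANS and mostly rescued successfully, ITT and PP can both sit near zero difference while the technique on its own is worse. Under the stated assumptions, a 5-point excess of FANS crossover hides 4.25 points and a 10-point excess hides the whole 8.5-point margin. The ITT part shrinks if rescue works less well, and the sign reverses if mini-PCNL fails more often.

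No crossover or rescue rate is given, so neither direction nor size can be known in advance. What is certain from the text is that neither stated analysis counts technical failure against the assigned procedure when rescue succeeds. The claim in Section 6 is therefore unsupported for this failure mode. The number of patients affected also stays unclear while Sections 5.7.2 and 5.10 differ on what follows a failed sheath placement.

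**What to change.** Keep ITT by assigned arm as the primary analysis. Add to Section 5.12 a prespecified key sensitivity analysis in all randomised patients, by assigned arm, in which any intraoperative crossover in either arm counts as not stone-free. Compare its 95% CI with the −8.5-point margin and report it beside ITT, with the number of crossovers and reasons per arm. Call a non-inferiority claim about the FANS technique itself robust only if this analysis agrees. In Sections 5.12 and 6, stop citing the PP exclusion of crossovers as the check for technical failure.

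Reconcile Sections 5.7.2 and 5.10 so that it is clear which patients with failed sheath placement count as crossovers. Settle all of this before any unblinding.

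The cost is wording only, since crossovers and reasons are already recorded. The claim becomes harder to support if FANS failures are common. The added analysis also has somewhat less power even when failures are balanced (72.0% against 80.1% at 5% in each arm).

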### Sample size

5.11

Based on published literature, the immediate SFR for mini‐PCNL in 1–2 cm lower pole stones is approximately 85%; we therefore assume an immediate SFR of 85% for both the mini‐PCNL and FANS f‐URS arms^8^, ^17^, ^18^. A non‐inferiority margin of 8.5% has been selected, as an absolute reduction in SFR of up to 8.5% is deemed the maximum clinically acceptable loss of efficacy given the benefits of FANS f‐URS (less invasiveness, faster recovery and lower bleeding risk) and aligns with margins used in similar endourological trials.^8^ Using simulations conducted in Stata with an 80% power and an alpha level of 2.5%, the required sample size is 278 participants per group (totalling 556). To account for an anticipated 15% loss to follow‐up or withdrawal, we inflate each arm to 320 participants, yielding a final enrolment target of 640 patients.

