**Patients and Methods:**

A total of 640 adults with CT‐confirmed 1–2 cm lower pole renal stones will be randomized 1:1 to undergo FANS‐f‐URS or mini‐PCNL across 20 high‐volume urology centres worldwide. Randomization is centralized and stratified by site. Radiologists and statisticians will remain blinded to allocation. Sample size was calculated assuming an 85% SFR for both arms, an 8.5% non‐inferiority margin, 80% power and 15% attrition. Analyses will follow both intention‐to‐treat and per‐protocol principles.

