### Randomization and allocation

5.5

Participants at respective institutions will be randomized in a 1:1 ratio to either the FANS f‐URS or mini‐PCNL arm, with each site enrolling 32 patients. Randomization will be performed centrally via a secure web‐based system at the time of enrolment, using computer‐generated permuted‐block sequences of varying sizes to maintain allocation concealment. Stratification by centre ensures balance across sites, and block sizes will be kept confidential. Investigators will obtain treatment assignments directly from the web application only after the patient's eligibility and consent have been confirmed.

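### Section 5.11 multiplies the 15% attrition allowance on instead of dividing it out, so 640 patients cover about 13% loss at 80% power, not 15% (minor)

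*Protocol article*

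**What the plan says.** Section 5.11 (Sample size) of the protocol article sets the assumptions: "we therefore assume an immediate SFR of 85% for both the mini‐PCNL and FANS f‐URS arms", and "A non‐inferiority margin of 8.5% has been selected", as an absolute difference. Power is 80% and alpha 2.5%, and the article says the number was obtained by simulation in Stata. The result is "the required sample size is 278 participants per group (totalling 556"). The attrition step follows: "To account for an anticipated 15% loss to follow‐up or withdrawal, we inflate each arm to 320 participants", which gives the enrolment target of 640. The formula for this step is not given.

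The abstract (Patients and Methods) repeats 640 patients, the 85% rate and the 8.5% margin, with "80% power and 15% attrition".

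Two other sections bear on the point. Section 5.12 makes the primary analysis intention to treat in everyone randomized, with a secondary per-protocol analysis. Section 5.10 keeps patients lost to follow-up in the trial and plans continued outcome collection where possible.

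**The concern.** An attrition allowance has one purpose: after the expected loss, the number left should still meet the requirement. If a fraction d of those enrolled is lost, the number left is N(1 − d), so N must be n / (1 − d). Multiplying by (1 + d) gives too small a figure, and 320 is exactly what that multiplication produces from 278.

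At stake is the accuracy of a headline design statement. Sample size, attrition and power are presented as one consistent set, in Section 5.11 and in the abstract, and the set will probably be carried into the results report. A reader who takes 15% of 640 away arrives at a number below the one that the same paragraph calls required.

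**Working it through.** **Inputs**, all from the protocol article:
- stone-free rate 85% in both arms, margin 8.5 points, power 80%, alpha 2.5%, attrition 15% (Section 5.11);
- 1:1 allocation (Section 5.5: "randomized in a 1:1 ratio to either the FANS f‐URS or mini‐PCNL arm");
- one-sided use of the 2.5%. This is not stated in words. It is inferred because it reproduces 278 and fits the analysis in Section 5.12: "Statistical results will be reported as estimates with 95% confidence intervals (CIs), which will be compared to the pre‐specified non‐inferiority margin".

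**Step 1: reproduce the requirement.** Normal approximation, unpooled variance, true difference zero:

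n per arm = (z₀.₉₇₅ + z₀.₈₀)² × 2p(1 − p) / margin²
= (1.95996 + 0.84162)² × 2 × 0.85 × 0.15 / 0.085²
= 7.8489 × 0.255 / 0.007225 = 277.02, rounded up to **278**.

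This matches the article exactly.

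**Step 2: reproduce the enrolment figure.**
- Multiplying on: 278 × 1.15 = 319.7, rounded up to **320** per arm, 640 in total. This matches the article exactly.
- Dividing out: 278 / 0.85 = 327.06, rounded up to **328** per arm, 656 in total. Inflating the total at once gives 556 / 0.85 = 654.1, so 655.

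The target is therefore 15 or 16 patients (about 2.5%) below the figure that a 15% loss calls for.

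**Step 3: what 640 leaves after 15% loss.** 320 × 0.85 = 272 per arm, 544 in total. Against the requirement: 278 − 272 = 6 per arm, 556 − 544 = 12 overall.

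**Step 4: the loss that 640 does cover.** 1 − 278 / 320 = **13.1%**.

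**Step 5: power**, by the formula that gives 278: power = Φ(0.085 / √(0.255 / n) − 1.960).

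| Analysed per arm | Situation | 0.085 / SE | Power |
|---|---|---|---|
| 272 | 640 enrolled, 15% not analysed | 2.776 | 79.3% |
| 278 | stated requirement | 2.807 | 80.1% |
| 320 | all 640 analysed | 3.011 | 85.3% |

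Two checks by other methods at 272 per arm: exact binomial enumeration of the 95% Wald interval gives 79.4% (80.4% at 278), and the Farrington–Manning score formula gives 78.3% (79.1% at 278). The size of the drop is similar by every method, about one point or less.

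**The case against.** The arithmetic is not open to dispute, but its consequence is, and most of what can be said on that side stands.

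- **The primary analysis is intention to treat in all randomized patients.** If all 640 contribute an outcome at the assumed rate, power is 85.3% and there is no shortfall. The 272 per arm applies only if patients without a primary outcome are left out. The article does not say how a missing CT is handled, so neither case can be taken for granted. This makes the power loss conditional. It does not rescue the attrition sentence, whose stated purpose is to allow for loss; if loss did not reduce the number analysed, no inflation would be needed.
- **The primary endpoint is early.** It is a CT within 72 hours of surgery, whereas follow-up runs to one month. Loss at 72 hours may well be below 15%, and 640 is enough up to 13.1%. That is a reason to expect little harm in practice, but it does not make the printed figures agree.
- **The gap is small against the precision of the method.** The article says 278 came from simulation and does not give the number of replicates. Assuming 1,000 replicates, the standard error at 80% power is √(0.8 × 0.2 / 1000) = 1.3 points; with 10,000 it is 0.4 points. A gap of 0.7 points lies within or near that. By the Farrington–Manning formula even 278 gives slightly less than 80%.

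A reader might infer more than the document supports:
- *That the trial misses its 80% power.* It does so only in the complete-case situation, and by less than one point on the plan's own formula.
- *That the plan promises 556 evaluable patients.* It gives 556 as the number required and does not say that 556 will remain.
- *That the per-protocol analysis is badly short.* Excluding crossovers and major violators will reduce it further, but the article gives no rate for these exclusions and makes no power claim for that secondary analysis.

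**Conclusion.** The point holds as a minor arithmetic error in a stated design figure. The 15% was multiplied on. With 15% of 640 lost and not analysed, 544 patients remain against a requirement of 556, with power about 79.3% instead of 80%. The enrolment target of 640 protects the required number up to about 13% loss.

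This rests on the article's own inputs, on reading alpha 2.5% as one-sided, and, for the power figure, on unevaluable patients being dropped. That 320 came from multiplication is inferred from the exact match. The shortfall itself does not depend on that inference, since 320 × 0.85 is 272 however 320 was reached. The error does not weaken the trial materially and does not call for more patients.

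**What to change.** Keep 640, which also equals the 20 sites × 32 patients of Sections 5.3 and 5.5. Restate the attrition sentence in Section 5.11 in one of two ways:
- 640 patients (320 per arm) allow for about 13% attrition while keeping 278 per arm and 80% power; or
- with 15% attrition, 640 patients leave 272 per arm and about 79% power.

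It would help to add that power is about 85% if all 640 are analysed with an outcome. Align the attrition wording in the abstract with the option chosen.

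The cost is one sentence in Section 5.11 and a few words in the abstract. Enrolment, site quotas, timeline and analysis do not change; one stated figure becomes slightly less favourable.
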